### Dropout from online treatments

A problem that has faced online treatments in general, and more particularly self-administered treatments without support, is that of dropout [60]. Dropout is a continued cause of concern as it is suggested that completing the entire course will benefit users, although several online studies have reported benefits for users who have not completed the entire course of treatment [61]. Some studies have collected information regarding dropout, suggesting difficulties using the computer, negative features of the program, perceiving the course as too demanding, poor clinical progress, receiving alternative treatment, feeling better, lack of time, and problems understanding the computer program [42,62]. The technology used in the current study has been specifically designed to include a number of engagement strategies for improving the user experience: personal, interactive, supportive, and social. An investigation of dropout will be valuable in assessing the user’s experience of online delivery.

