### Waiting list control

Participants in the waiting list control group will not receive any treatment for the duration of the intervention for the immediate treatment group (six weeks). At week seven the waiting list participants will be given access to treatment under the same conditions as the immediate treatment group received (Figure 1).

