### Assessments

At baseline, assessments (see Table 2) including Sociodemographics & History Questionnaire, Generalized Anxiety Disorder-7 (GAD-7), Penn State Worry Questionnaire (PSWQ), Beck Depression Inventory (BDI-II), Work and Social Adjustment Scale (WSAS), and EuroQol (ED-Q5) will be completed for screening purposes. Thereafter the GAD-7, PSWQ, BDI-II, ED-Q5 and WSAS will be completed at the end of treatment, week six (for both the active treatment group and the waiting list participants). The active treatment group will complete GAD-7, PSWQ, BDI-II, ED-Q5 and WSAS at the first follow-up, week 12 (three months). After each session supporters will provide post-session feedback. Thereafter participants will be asked to complete the Helpful Aspects of Therapy Form (HAT). The measure Satisfaction with Treatment (SAT) will be administered at week six.

**Table 2 T2:** Study measures to be used

**Measure**	**Assessment**	**Time of assessment**
Generalized Anxiety Disorder-7 (GAD-7)	Anxiety symptoms	Baseline, post-treatment and follow-up
Sociodemographic & History Questionnaire	Gender, age, marital status, education, occupation, socioeconomic status, and history	Baseline
Penn State Worry Questionnaire (PSWQ)	Symptoms of anxious worry	Baseline, Post-treatment and follow-up
Beck Depression Inventory (BDI-II)	Depression symptoms	Baseline, post-treatment and follow-up
EuroQol (EQ-5D-5 L)	Quality of Life indicators	Baseline, post-treatment and follow-up
Work and Social Adjustment Scale (WSAS)	Work and Social Adjustment scale	Baseline, post-treatment and follow-up
Engagement and Usage data	Engagement and usage	Continuous
Satisfaction with Treatment (SAT)	Satisfaction with therapy	Post-treatment
Helpful and Hindering Aspects of Therapy (HAT)	Helpful and hindering aspects of therapy	After each session

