### Planned statistical analysis

The analyses will be based on the intention-to-treat principle, including those who began treatment and provided follow-up data irrespective of treatment compliance. Missing data will be handled using Last Observation Carried Forward (LOCF). Effects will be tested at the 0.05 level. Analysis of variance (ANOVA)will be used to investigate any baseline demographic or clinical differences between the groups.

To test the main hypotheses, repeated measures ANOVA will be performed for the primary outcome measure for anxiety (GAD-7). Thereafter ANOVAs will be executed for the BDI-II, PSWQ, EQ-5D and WSAS. Contrasts will be conducted comparing changes from baseline to post-treatment for each group separately. Further analysis of baseline demographic variables and any relation to outcomes will be conducted. Effect sizes (Cohen’s d) will be calculated both within and between groups, based on the pooled standard deviation. For Cohen's d an effect size of 0.2 to 0.3 can be considered a small effect, around 0.5 a medium effect, and 0.8 upwards a large effect [83].

Analysis will be made to determine the proportion of participants who make a clinically meaningful change at the end of treatment and at follow-up. Pre-treatment, post-treatment, and follow-up GAD-7, BDI-II and PSWQ scores will be compared with clinical cutoffs to provide an indicator of remission. Remission is defined as the number of participants who initially scored at or above the established clinical cutoffs, and then at post-treatment and follow-up scored below the established clinical cutoffs: GAD-7 total score <10 [67]; BDI-II total score <14 [84], PSWQ <45 [85], and WSAS <10 [79]. In addition, we will calculate the relative risk of anxiety and depression by dividing the event rate (anxiety or depression) post-treatment by the event rate pre-treatment [70]. An estimation of recovery will be made by identifying the number of participants in each group who demonstrated a reduction of 50% of pre-treatment GAD-7, BDI-II and PSWQ scores [70]. In addition we will also calculate the number of reliably changed and recovered participants using Jacobson and Truax’s [86] criteria.

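### LOCF at week 6, the only controlled post-baseline visit, imputes zero change, so the estimated treatment effect is distorted by the level and imbalance of dropout

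*Protocol article*

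**What the plan says.** The article fixes the method itself, under Planned statistical analysis: "Missing data will be handled using Last Observation Carried Forward (LOCF". It names no other approach to missing data. For the main hypothesis, "repeated measures ANOVA will be performed for the primary outcome measure for anxiety (GAD-7". The sentence before the LOCF statement describes the intention-to-treat analysis as "including those who began treatment and provided follow-up data irrespective of treatment compliance".

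The visit schedule is under Assessments. Table 2 lists GAD-7 at "Baseline, post-treatment and follow-up", with no weekly GAD-7. The post-treatment assessment is at the "end of treatment, week six (for both the active treatment group and the waiting list participants". After that, "The active treatment group will complete GAD-7, PSWQ, BDI-II, ED-Q5 and WSAS at the first follow-up, week 12 (three months". The Waiting list control section adds: "At week seven the waiting list participants will be given access to treatment under the same conditions".

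On loss of participants, the section on dropout says "Dropout is a continued cause of concern" but gives no rate for this trial or for either arm.

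**The concern.** Carrying an observation forward needs an intermediate observation to carry. Here there is none. Between randomisation and the only controlled outcome visit, the sole GAD-7 score on file is baseline, so LOCF becomes baseline carried forward and asserts that each missing person did not change at all.

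That assertion is doubtful in both arms. Entry requires a GAD-7 of 10 or more, so regression to the mean and natural recovery make some improvement plausible even on the waiting list. If zero is wrong in both arms, the error is weighted by each arm's dropout. Unequal loss is foreseeable, because one arm has a six-module programme to abandon and the other only waits.

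The mean difference, its p-value and Cohen's d are affected. So are the GAD-7 responder outcomes: a carried-forward baseline of 10 or more can be neither below 10 nor a 50% reduction, so every missing participant becomes a non-remitter and a non-recoverer by construction. The imputed values also enter the analysis as if they had been measured.

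**Working it through.** **Inputs from the article.** 50 per arm, d = 0.50, power 0.80 and alpha 0.05 (Sample size); GAD-7 of at least 10 at entry (Eligibility criteria); the visit schedule above.

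**Assumed inputs, because the article gives none.** GAD-7 SD 4.5; baseline to week-6 correlation 0.5; mean improvement 4.25 (active) and 2.0 (waiting list); missingness of 10% to 40% per arm. The true difference is 4.25 − 2.0 = 2.25, and 2.25/4.5 = 0.50, which matches the planned d.

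**The plan's own figure.** Using 2(zα + zβ)²/d²: one-sided, 8 × (1.645 + 0.842)² = 49.5, so 50 per arm; two-sided, 8 × (1.960 + 0.842)² = 62.8, so 63. The stated 50 reproduces only as a one-sided test with no allowance for dropout. Sidedness is a separate matter. What counts here is that the sample size has no margin for loss.

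**Expected LOCF estimate.** In an arm with mean improvement m and proportion q missing (unrelated to outcome), the mean recorded change is (1−q)·m + q·0. The between-arm estimate is therefore mA(1−qA) − mW(1−qW).

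| Missing, active/control | Calculation | LOCF estimate | True |
|---|---|---|---|
| 30%/30% | 4.25×0.70 − 2.0×0.70 = 2.975 − 1.400 | 1.575 | 2.25 |
| 40%/10% | 4.25×0.60 − 2.0×0.90 = 2.550 − 1.800 | 0.750 | 2.25 |
| 10%/30% | 4.25×0.90 − 2.0×0.70 = 3.825 − 1.400 | 2.425 | 2.25 |
| 40%/10%, both improve 2.0 | 2.0×0.60 − 2.0×0.90 | −0.60 | 0 |
| 10%/40%, both improve 2.0 | 2.0×0.90 − 2.0×0.60 | +0.60 | 0 |

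Simulation (4,000 replicates) agrees with the first three rows: about 1.6, 0.8 and 2.4.

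**Type I error at 40%/10%.** The SD of change is 4.5×√(2×(1−0.5)) = 4.5, so its variance is 20.25. The variance of the LOCF change is (1−q)(20.25 + m²) − [(1−q)m]².
- Active: 0.6×24.25 − 1.2² = 13.11.
- Control: 0.9×24.25 − 1.8² = 18.585.
- SE = √(31.695/50) = 0.796, and 0.60/0.796 = 0.754.
- Two-sided rejection at 0.05: Φ(−1.206) + Φ(−2.714) = 0.114 + 0.003 = 0.117. Simulation gives about 0.12.

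**Range.** With the same null, rejection is 0.05 at 30%/30% and 0.05 to 0.06 at 25%/20% and at 30%/20%. A separate run in SD units, with both arms improving 0.5 SD, gives 5.4% at 20%/20%, 14.1% at 40%/10% and 12.9% at 10%/40%.

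**Power, with the two causes separated.** At 30%/30% and a true difference of 2.25, two-sided power is 0.49 for LOCF change scores, 0.54 for change scores on observed data and 0.66 for baseline-adjusted ANCOVA on observed data. Of the 0.66 − 0.49 = 0.17 gap, 0.54 − 0.49 = 0.05 comes from LOCF and 0.12 from baseline adjustment. With almost no missing data, ANCOVA already leads by 0.81 to 0.71.

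**The case against.** The strongest objection is that the sentence on the analysis set governs. If only people with follow-up data are analysed, LOCF has little or nothing to fill at week 6, and the simulation does not describe this plan. That stands as a limit on how firmly the size of the bias can be stated. It does not rescue the plan, because randomised participants are then excluded under an intention-to-treat label. The two sentences cannot both operate fully, and neither reading gives a sound primary analysis.

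A second objection is that the larger figures need marked imbalance, and that the section on dropout mainly concerns unsupported programmes, whereas this trial provides weekly support. Stopping the programme is also not the same as missing the week-6 questionnaire. This stands: with modest imbalance, type I error stays near 5%. Attenuation of a real effect, however, needs no imbalance.

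Some stronger readings are tempting but not supported:
- A reader might infer that the estimate reflects dropout instead of treatment. The formula contains both arms' improvements, so the treatment effect is distorted, not replaced.
- A reader might infer that type I error is inflated generally. That requires unequal dropout together with improvement in both arms.
- A reader might credit the whole power gain of an adjusted model to dropping LOCF. Most of it at 30%/30% comes from baseline adjustment.
- A reader might infer that waiting-list week-6 scores will be carried to week 12 in a three-time-point comparison. The article states no such analysis; its contrasts run from baseline to post-treatment.

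Nor can LOCF be defended as always conservative: at 10%/30% it overstates the effect, though only by 2.425/2.25, about 8%.

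**Conclusion.** The point holds as a matter of design. At the single controlled follow-up visit, LOCF is baseline carried forward. It sets missing participants' change to zero and counts them as GAD-7 non-remitters and non-recoverers. The direction and form of the distortion follow from the schedule and the stated method alone.

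The size is conditional. It depends on dropout rates and mean improvements that the article does not give, on missingness unrelated to outcome, and on the LOCF sentence prevailing over the restriction to people with follow-up data. Under the assumed values, a true 2.25 points is estimated at 0.75 to 2.43, and a true null is rejected about 12% of the time when 40% and 10% are missing. With equal dropout the null is unbiased and a real effect shrinks by (1−q).

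This affects the primary analysis and should be corrected before outcome data are analysed.

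**What to change.** 1. Define the primary analysis set as all randomised participants, and remove the condition on starting treatment and providing follow-up data. Everyone randomised has a baseline GAD-7, because screening is scored before allocation.
2. Replace LOCF in the primary analysis with either a likelihood-based mixed model on baseline and week 6 with a group-by-time term, or multiple imputation by arm followed by baseline-adjusted ANCOVA.
3. With multiple imputation, use the same imputations for the remission and 50%-reduction outcomes, so that missing people are not classed as failures by default.
4. Keep LOCF, if wanted, only as a labelled sensitivity analysis, and add one that probes departures from missing at random.
5. State that week-12 data come from the active arm only and are analysed as an uncontrolled within-arm comparison.

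The cost is analysis wording and standard software, with no new data. The replacement rests on a missing-at-random assumption, which the added sensitivity analysis can examine. Recruitment is already under way, so the change should be dated and recorded before outcomes are examined by arm.

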### Sample size

Previous studies of online interventions for GAD that have used a CBT protocol similar to the intervention in the current study have reported post-treatment effect sizes of between 0.79 and 1.67, and follow-up effects of between 0.69 and 1.65, based on sample sizes ranging from 10 to 97 [33,48-50]. We calculated power using G-Power software [66]. Using a power of 0.80 and an alpha of 0.05, we would need 50 subjects in each arm of the trial to observe a moderate (*d* = 0.50) post-treatment difference on the main outcomes.

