### Randomization

Using computer algorithms to score screening instruments at baseline, participants will be automatically randomized to either the active intervention group or a waiting list control group. Participants will be immediately informed about the randomization outcome. The randomization procedure will be managed by a person independent of the research group.

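### Baseline ANOVA at the 0.05 level is the wrong test for multi-category nominal variables and, among all those randomised, does not show whether an imbalance matters

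*Protocol article*

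**What the plan says.** Planned statistical analysis sets a general level, "Effects will be tested at the 0.05 level", and the next sentence says that ANOVA "will be used to investigate any baseline demographic or clinical differences between the groups". No other method is named for any baseline variable.

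Table 2, under Assessments, lists the content of the sociodemographic questionnaire: "Gender, age, marital status, education, occupation, socioeconomic status, and history". The same section has five scales (GAD-7, PSWQ, BDI-II, WSAS and EuroQol) completed at baseline and repeated later.

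Under Randomization, "participants will be automatically randomized to either the active intervention group or a waiting list control group".

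A later paragraph of the analysis section adds: "Further analysis of baseline demographic variables and any relation to outcomes will be conducted".

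**The concern.** The article fixes a method here, so this is not detail left to an unseen analysis plan. The method has two faults.

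- ANOVA compares means. A variable such as marital status has no mean until someone assigns numbers to its categories, and the assignment is arbitrary.
- Allocation is random, so among all those randomised the null hypothesis of a baseline test is true by design. The p-value then measures how surprising a chance difference is. It does not measure whether the difference is large enough, on a variable prognostic enough, to matter.

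At stake is how the trial is read. A chance significant result can cast doubt on a sound randomisation, and a non-significant result can be taken as reassurance that it does not provide.

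**Working it through.** **Inputs.** From the article: level 0.05 (Planned statistical analysis); 50 per arm and target d = 0.50 (Sample size); six named demographics and five scales (Assessments and Table 2), so 11 countable variables, leaving out the uncounted history items. Assumed, because the article gives no figure: independence of the tests, a baseline-to-outcome slope of 0.3 to 0.7, and the category counts in step 1.

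The article gives no figure for the baseline comparisons themselves. Its 50 per arm is used here as stated. That number reproduces for a one-sided test, 2 × (1.645 + 0.842)² / 0.50² = 49.5, so 50; a two-sided test gives 63. This is a separate matter and does not affect what follows.

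**Step 1: nominal variables.** Take a three-category variable with counts 10/30/10 in one arm and 20/10/20 in the other.

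- Codes 1, 2, 3: the means are (10 + 60 + 30)/50 = 2.0 and (20 + 20 + 60)/50 = 2.0, so F = 0 and p = 1.00.
- First two codes swapped (2, 1, 3): the means are (20 + 30 + 30)/50 = 1.6 and (40 + 10 + 60)/50 = 2.2. Between-group sum of squares = 25 × 0.6² = 9. Within-group sum of squares = 32 + 28 = 60 on 98 df. F = 9 / (60/98) = 14.7, p = 0.0002.
- Chi-square, with expected counts 15/20/15 in each arm: 4 × 25/15 + 2 × 100/20 = 16.67 on 2 df, p = 0.0002.

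The data are identical, and the ANOVA answer is set by the coding. A simulation with shares 20/60/20 against 40/20/40 and 50 per arm (4,000 runs) gives rejection rates of 5% with codes 1, 2, 3, 97% after relabelling, and 98% for chi-square. For a binary variable the two tests agree: 5.0% each under the null, and 60% each for 60% against 80%.

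**Step 2: false alarms.** P(at least one) = 1 − 0.95^k. For the five scales alone this is 23%; for k = 11 it is 1 − 0.95^11 = 43%.

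**Step 3: what passes as non-significant.** The smallest significant gap is t(0.975, 98 df) × √(2/50) = 1.984 × 0.2 = 0.397 SD.

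**Step 4: what a gap of that size would do.** Conditional on a baseline GAD-7 gap of 0.40 SD, a comparison of week-six scores alone shifts by slope × 0.40, which is 0.12 to 0.28 SD, or 24% to 56% of d = 0.50. The group-by-time contrast of a baseline and week-six repeated measures ANOVA is a comparison of changes. It shifts by (1 − slope) × 0.40 in the opposite direction: 0.28 SD at slope 0.3 and 0.12 SD at slope 0.7. At a gap of 0.39 SD the conditional type I error of that contrast is 0.10 to 0.16; at a gap of 0.2 SD it is about 0.05.

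**The case against.** The case for treating this as a minor reporting matter is strong, and much of it stands.

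- **Use of the tests.** A reader might infer that they will select covariates or establish equivalence. The article says neither. It says only that differences will be investigated, and the sentence on demographics and outcomes stands in another paragraph with no link to the baseline tests.
- **Bias.** A reader might infer from step 4 that the treatment effect will be biased. Across randomisations the estimator is unbiased. A gap of about 0.40 SD or more on a given variable arises in only 5% of sound randomisations. The average absolute gap is 0.2 × 0.80 = 0.16 SD, which at slope 0.5 moves a week-six comparison by 0.08 SD. The shift is also the same whether or not a baseline test is run: covariate adjustment removes it, and deleting the test does not.
- **Scope of the nominal error.** Gender with two categories is unaffected, and education has a natural order. Marital status and occupation remain, in a sample of registered students. The example in step 1 was built to make the point and would be very rare under randomisation.
- **False-alarm rate.** The 43% assumes independence, although the anxiety, worry and depression scores are likely to be correlated. A false alarm does not in itself change the type I error of the primary test.
- **Chance as the only cause.** The analysis set is limited to people who started treatment and gave follow-up data. If the baseline comparison is run in that set, differences may also reflect selection after randomisation. This is a fair limit on the argument, but it does not rescue the test: at 50 per arm its power to flag a 0.3 SD difference is 32%.

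None of this answers the two basic faults: the wrong test for multi-category nominal variables, and a p-value that does not address importance for the rest.

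**Conclusion.** The point holds in a limited form. The stated baseline method gives coding-dependent results for unordered variables with three or more categories. For every variable compared among all those randomised, it does not show whether an imbalance matters. Its operating characteristics are about a 43% chance of at least one false alarm over 11 variables (independence assumed) and non-significance for any gap below about 0.40 SD at 50 per arm. The 0.12 to 0.28 SD shift is conditional on a gap at that limit and on an assumed slope of 0.3 to 0.7; it is not an expected bias. No primary estimate, error rate or sample size changes because of this sentence, but the correction is specific and nearly free, so it should be made.

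**What to change.** Replace the baseline ANOVA sentence with text to this effect:

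> Baseline characteristics will be tabulated by randomised arm as mean and SD, or n and %, without significance tests. Imbalance will be judged by its size and by the prognostic relevance of the variable. Each outcome comparison will be adjusted for the baseline value of that outcome, whatever the observed balance. Analyses relating demographic variables to outcomes are exploratory.

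The baseline scores are already collected, so data collection does not change. Trial status reports a second round of recruitment just beginning, so the change could be made before analysis. What is lost is a column of p-values. Adjustment costs essentially no precision: the variance factor is 1 − r² for the adjusted comparison against 2(1 − r) for change scores, for example 0.75 against 1.00 at an assumed correlation of 0.5.

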## Discussion

This study seeks to evaluate the effectiveness of an internet-delivered treatment for GAD in a sample of students in Ireland. The study will be a contribution to the potential for a low-intensity internet-delivered program implemented in a service-based setting. The study will be a contribution to the already established work in online treatments for anxiety worldwide.

The primary outcome measure (GAD-7) that will assess anxiety symptoms is a well-established measure and has been used in previous trials involving internet-delivered and face-to-face treatments. The secondary outcome measures (BDI-II, PSWQ) will each give an insight into participant’s improvements, principally in pathological worry (a central construct in GAD) and any corresponding improvements in comorbid depressive symptoms. The WSAS and ED-Q5 will assess any improvements in quality of life indicators corresponding to improvements in anxiety symptoms for participants.

The other secondary outcome measures (HAT, SAT) that we have included in the study will contribute to what participants find satisfying with online treatments and further will detail what in-session events and their impacts participants report as being helpful or hindering in their online treatments [82,88].

It is also hoped that with the inclusion of pre-treatment and during treatment dropout questionnaires, the study can make a contribution to developing a better understanding of the reasons for dropout in online treatments.

The results may not be generalizable to the wider community in Ireland, but perhaps may give insight into the usefulness of low-intensity internet-delivered interventions within a stepped-care model in routine primary care. The internet-based intervention is interesting for adult students who are high users of the internet and related tools, who look for alternative healthcare [53] as a preference, and because the possibility of accessing traditional services is difficult, prohibitive due to waiting lists, costs, and personal stigma.

